### Disease and Data

We use Swedish clinical notes in the gastrointestinal (gastro) domain in our study. The data used are from the gastrointestinal department of the Health Bank infrastructure at Stockholm University [11]. The data contain both in- and outpatient records of patients receiving treatment at the department, both surgery and other medical interventions. The data originate from a hospital, and no effort was made to include only similar cases; therefore, the cases vary.

The data are pseudonymized and have been curated by 2 professional clinical coders, so as to double-check the coding and create a gold standard. The 2 coders reviewed the data independently and reconciled their differences through discussion. This curation process also ensures that it will be possible to assign a code based on the clinical text alone, without the need for further information about the patient. This is important since the user study will not have access to further EHR data such as laboratory results or drug lists.

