### Study Design

This study is designed as a 2×2 crossover study as illustrated in Figure 1. This design, AB|BA (2 different sequences and 2 periods), is chosen for its uniform and balanced properties, aiming to control the carryover effect between periods. The design is suitable not only for comparing treatments but also for assessing pre-post effect of an intervention [26]. In addition, the crossover design requires a comparatively smaller number of participants than what a randomized controlled trial would ordinarily require.

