**Figure 1 figure1:**
[figure not shown]
Crossover randomized controlled trial where study participants are randomized into 2 groups. The first group first uses a control interface and then switches to our Easy-ICD tool, while the second group starts with our tool and switches to a control interface.

We will not incorporate a washout period partly because the learning element in the tasks measured is limited and partly because we do not want to risk losing participants in a long break between periods. The data sets in the 2 periods are different, and this limits any carryover effect in the sense that coders cannot memorize the text or the correct codes.

Once participants are recruited, they are randomly allocated to the 2 groups without allocation concealment. Allocation concealment will not be relevant for coders since it is known whether a participant is assisted or not, and we will not develop a placebo coding assistant. We will, however, conceal the allocation of subjects for the analyses.

In total, participants will code 20 clinical notes, where each note belongs to a single patient. The participants are asked to complete the experiment in 1 sitting without interruptions, and they cannot revisit or go back to previous notes. In the event that participants are interrupted, they are asked to exit the experiment, and any incomplete experiments are discarded as invalid.

In terms of the coding process, both the control and intervention user interfaces have a search utility for looking up *ICD-10* codes. Participants will be free to access any other additional search tools they wish to use without restriction. Since we measure time using a before and after design, the effect of additional tools is not expected to be a significant factor. The time is logged based on the browser button presses such as “Start,” “Next,” and “Complete.”

The user study process can be summarized in the following steps:

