Study participants are randomly allocated to group 1 and group 2.To prepare participants for the experiment, a short video tutorial is played after the consent form is signed and right before the clinical coding task commences.In period 1 with 10 clinical notes, group 1 uses the control interface, while group 2 uses the intervention interface.Data are logged in the background using button presses—time, assigned codes, and comments.Then, there is an immediate crossover to period 2 for the last 10 clinical notes.Data continue to be logged in the background using button presses.At the end, participants in both groups will complete the system usability scale.

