### Measurements and Analyses

The focus of our measurements is on how clinical coders perform with and without our system:

Compared with the performance of the unaided user, statistical tests of significance are used to check whether there are significant differences in the quality of coding when Easy-ICD is used, as measured by accuracy and *F*_1_-score.Time spent is the time it takes for a clinical coder to assign a code.System usability survey will be given to all participants to measure usability of the web interfaces, both with and without our Easy-ICD system.

Main analyses are based on hypothesis testing using the paired *t* test and Wilcoxon test to compare the before and after means at a significance level of .05. Table 1 summarizes these hypotheses based on a test of equivalence.

**Table 1 table1:** Time use and coding quality hypotheses testing to compare the before and after means.

Time use		Coding quality (accuracy and *F*_1_-score)

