**Alternative hypothesis: (H_1_: μ_1_≠μ_2_)**		
	There is a significant time difference between using CAC and not using CAC for coding Swedish clinical notes	CAC affects a clinical coder’s coding quality by a significant margin

^a^CAC: computer-assisted clinical coding.

In additional exploratory analyses, we will examine the effect wrong suggestions have on the coder’s performance, and how often coders adopt these wrong suggestions. In addition, the distribution of the different professions between the groups as well as the coding experience will be explored.

To enable us to analyze the main outcomes in relation to text complexity, we distinguish between two categories of clinical texts: (1) short and simple texts (<512 tokens) and (2) long and complex texts (>512 tokens). However, we only consider the length of the text as the complexity dimension, as opposed to the complexity of the case or provided care, for example.

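### The main paired test ignores period although each period has its own notes, so a difference between note sets costs power and, if the sequences end up unequal, shifts the estimated tool effect

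*Protocol article*

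**What the plan says.** Study Design describes a 2×2 crossover: "This design, AB|BA (2 different sequences and 2 periods), is chosen for its uniform and balanced properties". The process steps say: "In period 1 with 10 clinical notes, group 1 uses the control interface". Group 2 has the tool in that period, and there follows an "immediate crossover to period 2 for the last 10 clinical notes". On the notes themselves it says: "The data sets in the 2 periods are different, and this limits any carryover effect". The only randomisation described is of coders to the two groups. No ratio or blocking is given, and incomplete experiments are discarded.

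Disease and Data says of the source records that "no effort was made to include only similar cases; therefore, the cases vary". Evaluation Outcomes expects the largest time savings on long texts.

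Measurements and Analyses bases the main comparison on a paired t test and a "Wilcoxon test to compare the before and after means at a significance level of .05". It mentions no term for period, sequence or note set.

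**The concern.** Group 1 meets the tool only on the second set of notes and group 2 only on the first. If one set is harder, or if coders speed up or tire between periods, that difference is part of every coder's tool-minus-control difference. It is positive in one group and negative in the other.

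An AB|BA design can remove such a difference, but only if the analysis uses the sequence structure. A pooled paired test does not. It treats the set difference as random scatter between coders, and its estimate cancels the difference only when the sequences are equal in size. At stake are power in a study of at most 30 coders and, after an uneven split, the size of the reported tool effect. The algebra is the same for time, accuracy and F1-score.

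**Working it through.** **The plan's own figure.** The total of 30 cannot be strictly reproduced, because the effect sizes and target power appear only in Figure 2, which is not shown. It agrees with a standardised effect of 0.8 and 80% power: a paired two-sided t test at 5% then needs n = 15 (power 82.1%), doubled to 30. That calculation has no allowance for a set or period difference.

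**Model.** Let D be tool minus control for one coder, tau the tool effect, and pi the period 2 minus period 1 difference, which includes the difference between sets.
- Group 1 (tool in period 2): D = tau + pi + error.
- Group 2 (tool in period 1): D = tau − pi + error.
- Pooled mean: tau + pi(n1 − n2)/N.
- Added variance of D: about 4·n1·n2·pi²/N², which is pi² when n1 = n2.

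**Assumed inputs (log time; none is in the documents).** Residual SD 0.5 per note, 10 notes per period, coder-by-interface SD 0.15 on the difference, true saving 15%.
- SD(D) = √(2×0.5²/10 + 0.15²) = √0.0725 = 0.269.
- tau = ln 0.85 = −0.163, so the standardised effect is 0.163/0.269 = 0.60.

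**Assumed gap.** With a between-note SD of 0.3, half the notes long, and long notes taking twice as long, two random sets of 10 differ in mean with SD √(0.2×(0.3² + 0.25×(ln 2)²)) = 0.205. If length is balanced between the sets, this is √(0.2×0.3²) = 0.134.

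**Equal sequences, 15/15.** At a gap of 0.2 the SD used by the paired test rises to about √(0.0725 + 0.04) = 0.335. The typical |t| falls from 0.163/(0.269/√30) = 3.31 to 0.163/(0.335/√30) = 2.65. Simulated rejection rates:

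| Gap | Paired: power | Paired: type I error | Period-adjusted: power | Period-adjusted: type I error |
|---|---|---|---|---|
| 0 | 89% | 5% | 89% | 5% |
| 0.134 | 84% | 3% | 89% | 5% |
| 0.2 | 77% | 1.5% | 89% | 5% |
| 0.3 | 59% | 0.3% | 89% | 5% |

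**Unequal sequences, 19/11, gap 0.2.**
- Shift: 0.2×(19 − 11)/30 = 0.053, about a third of the true effect (0.053/0.163).
- If group 1 is the larger, the mean estimate is −0.163 + 0.053 = −0.109 (to rounding) when set 2 is harder, or −0.216 when set 1 is harder. As savings these are 1 − exp(−0.109) = 10% and 1 − exp(−0.216) = 19%.
- Power of the paired test is 39% or 96%, according to that direction.
- With no true effect, the paired test rejects in about 9% of trials.
- The period-adjusted test has no shift, 5% error and about 87% power.

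**How likely is an unequal split?** If randomisation is simple, 30 coders split 18:12 or worse with probability 36%, and 19:11 or worse with probability 20%, before any experiment is discarded.

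**The case against.** **The shared sets are inferred.** The article does not say that every coder sees the same 10 notes in a period. A web application that shuffles notes for each coder would also give different notes in the two periods. This stands as a limit: shared sets are the natural reading of the process steps, not an explicit statement. An ordinary period effect, such as practice or fatigue, would enter D in the same way even if notes were shuffled.

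**The crossover already protects the estimate.** Each set is coded under both interfaces by randomised groups. With equal sequences the pooled estimate is unbiased and the test errs on the safe side. This is correct, and the loss there is power only.

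**The error-rate figures are conditional.** A reader might infer that the plan inflates false positives generally. It does not. Averaged over simple randomisation, the paired test's type I error was 4.8–4.9% at gaps of 0.134, 0.2 and 0.3. The 9% applies only given a 19/11 split.

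**Stronger inferences that fail.**
- A reader might infer that tying notes to periods is what prevents a check on carryover. In any 2×2 crossover, carryover is aliased with sequence and with the interface-by-period interaction, whichever notes are used.
- A reader might infer that the short-versus-long comparison is confounded with set. That needs unequal length mixes, on which the article is silent.
- Sample Size Calculation could be read as testing within each sequence, which would confound set with tool completely. That sentence concerns sample size, and Measurements and Analyses does not describe such a test.

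**Conclusion.** The concern holds as a mismatch between design and analysis. The protocol gives each period its own notes from unmatched cases, then names a main test that cannot remove a difference between periods. With near-equal sequences the cost is a conservative test with less power: 89% to 77% at a gap of 0.2 log units, and 84% if the gap is the 0.134 expected with length balanced. With unequal sequences the estimate given that split is shifted by pi(n1 − n2)/N, in either direction.

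The formulas need only an additive period or set effect. The percentages rest on assumed SDs and an assumed gap and are illustrative. The documents do not support a claim that the tool effect is biased whatever the split, or that the crossover itself is invalid.

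**What to change.** **Main change, in the analysis.** Replace the plain paired t test with the period-adjusted crossover analysis. Take the mean tool-minus-control difference in each sequence, average the two means with equal weight, and use the pooled within-sequence SD. A mixed model with interface, period (set) and coder, and note where possible, serves the same purpose. In place of the Wilcoxon signed-rank test, compare within-coder period differences (period 2 minus period 1) between the two sequences with a rank-sum test. State in the protocol whether all coders receive the same notes in each period.

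The cost is 1 degree of freedom (29 to 28 with 30 coders) and a few sentences. No data already collected are lost.

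**Secondary change, for coders still to be recruited.** Put the same number of short and long notes in each set, and let the web application cross set with interface order so that set and period can be separated. Keep coders already enrolled and analyse them with the same terms. This needs a small software change and leaves two note orders in one data set, which the set and period terms handle.

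The analysis change comes first. Randomising notes to interface for each coder while keeping the plain paired test only turns the set gap into noise: the variance of D becomes 0.0725 + 2×0.3²/10 = 0.0905, and power is 79–81% under the same assumptions, against about 89% with the period-adjusted test on fixed sets.

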### Sample Size Calculation

This experiment is novel, and we have not succeeded in finding many similar studies from which to estimate test parameters. Therefore, our experiment is important in that it provides baselines that may be useful for similar experiments in the future. We do expect a correlation between periods; the same coders are measured twice on mean performance in time, making a matched 2-tailed *t* test suitable for the task [26]. This matched 2-tailed *t* test (period) is done in 2 sequences, and the sample size calculation must therefore be doubled [27]. Further, each sequence will consist of approximately 10 coding instances, giving extra power to the estimation of the sequence mean. Due to the unknown nature of the expected effect size, the sample calculation in Figure 2 is made with 3 different effect estimates ranging in the upper level of medium to high effect. A pilot study is necessary to establish a probable effect size and adjust sample size estimation if needed.

**Figure 2 figure2:**
[figure not shown]
Statistical power of a 2-tailed t test at the level of 5% depending on sample size per sequence (2-tailed t test with equal SD in both study sequences to compare means).

Based on the plot in Figure 2 derived from power analysis in G*Power [28], we aim to recruit up to 30 participants in total. Multiple methods are used to recruit participants, including contacting hospitals and health authorities directly, announcing at coding seminars and conferences, publishing news in popular science media, and advertising on social media groups and other electronic media.

### Measurements and Analyses

The focus of our measurements is on how clinical coders perform with and without our system:

Compared with the performance of the unaided user, statistical tests of significance are used to check whether there are significant differences in the quality of coding when Easy-ICD is used, as measured by accuracy and *F*_1_-score.Time spent is the time it takes for a clinical coder to assign a code.System usability survey will be given to all participants to measure usability of the web interfaces, both with and without our Easy-ICD system.

Main analyses are based on hypothesis testing using the paired *t* test and Wilcoxon test to compare the before and after means at a significance level of .05. Table 1 summarizes these hypotheses based on a test of equivalence.

**Table 1 table1:** Time use and coding quality hypotheses testing to compare the before and after means.

Time use		Coding quality (accuracy and *F*_1_-score)

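### The main paired tests take no account of period, although each period uses a different set of notes, so power is lost with equal sequences and the estimate shifts with unequal ones

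*Protocol article*

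**What the plan says.** Under Study Design the trial is a 2×2 crossover: "This design, AB|BA (2 different sequences and 2 periods), is chosen for its uniform and balanced properties". The procedure gives each period its own notes: "In period 1 with 10 clinical notes, group 1 uses the control interface, while group 2 uses the intervention interface", followed by an immediate switch for the last 10 notes. The different note sets are mentioned only as protection against carryover: "The data sets in the 2 periods are different, and this limits any carryover effect". Learning is called limited, not absent. Disease and Data says that the cases in the source data vary. Evaluation Outcomes says that long, complex texts take more resources than short ones.

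Under Measurements and Analyses the main tests are fixed: "using the paired *t* test and Wilcoxon test to compare the before and after means at a significance level of .05". Study Design uses the same idea for time: "Since we measure time using a before and after design". Table 1 states the hypotheses as using CAC versus not using CAC. Sample Size Calculation describes a matched test carried out in two sequences. It does not say how the sequences are combined so that a period effect drops out.

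**The concern.** In an AB|BA design the two sequences make it possible to separate the treatment effect from the period effect. A single paired test on CAC minus control does not use this. Group 1 has control first, so its mean difference contains the treatment effect plus the change from period 1 to period 2. Group 2 has CAC first, so its mean difference contains the treatment effect minus that change. Pooling the two groups puts the period effect into the error term and, if the groups differ in size, into the estimate as well. Both main comparisons, time and coding quality, rest on this test. The choice of main test is stated in the protocol; it is not a detail left to a later analysis plan.

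**Working it through.** **The protocol's own figure.** The total of up to 30 cannot be strictly reproduced, because the effect sizes and target power are in Figure 2, which is not shown. It is compatible with an assumed standardised paired difference of 0.8 at 80% power and two-sided 5%: n = 15 (power 82.1%), doubled to 30. Values of 0.7 and 0.9 would give 38 and 24.

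**Inputs.** From the protocol: N = 30, two-sided 5%, two sequences, a different note set per period. Assumed: the treatment effect τ and the period effect δ (period 2 minus period 1), both in SDs of the within-coder difference. τ = 0.53 is chosen because it gives about 80% power at N = 30 with no period effect; 0.7 and 0.8 are shown as larger alternatives.

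**Model.** CAC minus control has mean τ + δ in group 1 and τ − δ in group 2, with SD 1 within each group.

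**Equal sequences, 15/15.** The mean of all differences is τ, so there is no bias. Its true standard error is 1/√30 = 0.183. The paired test, however, estimates the variance as about 1 + δ²·30/29. For δ = 0.25, 0.5 and 1 this is 1.06, 1.26 and 2.03, so the standard error used is too large by factors of 1.03, 1.12 and 1.43. With no period effect the expected test statistic is 0.53·√30 = 2.90. It falls to about 2.81, 2.59 and 2.04, against a critical value of 2.05. Simulation gives:

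| δ | Paired power, τ = 0.53 | τ = 0.7 | τ = 0.8 | Paired type I error |
|---|---|---|---|---|
| 0 | 80% | 96% | 99% | 5% |
| 0.25 | about 79% | 95% | 99% | about 4% |
| 0.5 | 73% | 93–94% | 98% | about 3% |
| 1 | 50% | 81% | 92% | about 0.5% |

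The period-adjusted test holds 5% type I error, and at τ = 0.53 has 80% power, for every δ. The Wilcoxon test behaves like the paired t test (71% power at τ = 0.53, δ = 0.5).

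**Unequal sequences.** The paired estimate has mean τ + δ(n1 − n2)/N.
- 18/12: shift = δ·6/30 = 0.2δ. At δ = 0.5 the mean estimate is 0.53 + 0.10 = 0.63; with 12/18 it is 0.43. Type I error stays near 5%, because the inflated standard error offsets the shift.
- 20/10: shift = δ·10/30 = 0.33δ. Type I error is about 6% at δ = 0.25, 10% at δ = 0.5 and 17% at δ = 1.

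**How often.** The protocol names no ratio or blocking. If allocation were simple randomisation (an assumption), the binomial(30, 0.5) tails give 36% for 18/12 or worse and 9.9% for 20/10 or worse. Averaged over all such splits, type I error stays near 5%.

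**Adjusted test.** The estimate is half the sum of the two group means, with standard error ½√(1/n1 + 1/n2) and 28 df. This is 0.183, 0.186 and 0.194 at 15/15, 18/12 and 20/10. At τ = 0.53 power is about 80%, 78–79% and 75%.

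**The case against.** The strongest reply is that the harm is not shown to be large, and much of that stands. The size of δ is unknown. Different notes need not differ much in mean difficulty, and the remark that cases vary describes the source data, not how the two sets of 10 were built. The protocol implies, but does not state, that all coders see the same two sets in the same order; if sets were randomised per coder, only practice and fatigue would remain. At δ = 0.25 the balanced loss is 1 to 2 points. The 0.53 SD effect is an assumption, and the protocol speaks of upper-medium to high effects, where the loss is small unless δ is near 1 SD.

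A reader might infer three stronger things that the document does not support:
- That the before-and-after wording means period 1 versus period 2, which would cancel the treatment effect when sequences are balanced. Table 1 and the opening of Measurements and Analyses define the contrast as with versus without CAC, so this is loose wording.
- That the test is invalid in general. It is conservative when balanced and near 5% at 18/12; the inflation is conditional on a marked imbalance.
- That treating the notes as fixed inflates type I error by a known amount. Any such figure rests on assumed variance components that the protocol does not give.

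What does not stand is the suggestion that the two-sequence wording in Sample Size Calculation already deals with period: no method of combining the sequences that removes it is named. An analysis plan not shown could add one, but the main tests as stated do not.

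**Conclusion.** The concern holds in a limited form. The stated main tests ignore period in a design where the note set changes with period. The consequence with equal sequences is lost power: from 80% to about 79%, 73% and 50% at δ = 0.25, 0.5 and 1, for an assumed effect of 0.53 SD, and much less at 0.7 to 0.8 SD. With unequal sequences the estimate moves by δ(n1 − n2)/N in either direction, with clear type I inflation at 20/10 but not at 18/12. Discarding incomplete sessions could add to an imbalance, though no rate is given. These sizes rest on the assumed τ and δ, on N = 30, and on all coders receiving the same note sets in the same order.

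**What to change.** Make the main analysis of time and of coding quality a period-adjusted comparison of CAC with control. Either of these serves:
- a two-sample t test comparing within-coder period differences between the two sequences (half the difference in means estimates the treatment effect), with the rank-sum analogue in place of the Wilcoxon test; or
- a mixed model with interface, period and coder.

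Replace the before-and-after wording with CAC versus control, to match Table 1. Keep the unadjusted paired t and Wilcoxon tests as sensitivity analyses. State whether all coders receive the same two note sets in the same order.

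The two-sample version costs one degree of freedom (28 instead of 29). At an assumed 0.53 SD it leaves power at about 80% with equal sequences, 78–79% at 18/12 and 75% at 20/10. It uses data that are already logged. It removes a period effect common to both sequences but does not address differential carryover.

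Two further steps are optional: random note effects as a sensitivity analysis, and equal numbers of short and long notes in each period. The second is a design change, and recruitment has already begun.

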### Inclusion and Exclusion Criteria

In terms of participants, the main inclusion criterion is that the participant has coded clinical texts before, preferably *ICD-10* coding. Participants could be clinicians, nurses, professional coders, or other health care staff who understand Swedish with any amount of coding experience. We shall exclude participants outside Sweden or Norway.

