### Evaluation Outcomes

The evaluation outcomes are as follows: (1) clinical coders aided by our Easy-ICD system are expected to yield better performance, that is, the accuracy and *F*_1_-score. (2) We expect that the Easy-ICD system will result in time savings during coding tasks. Looking at the 2 categories of clinical notes, it can be expected that the most time savings could be gained with large and complex texts. Such cases take more resources than shorter and simpler texts. (3) We expect the usability of the system to have a system usability score over the generally accepted normal score of 68 [29]. Further, we do not expect any significant differences between the usability of the user interfaces with and without our CAC system.

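### Two tests decide each hypothesis at .05 with no rule if they disagree, both are described as comparing means, and the scale for coding time is left to raw means

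*Protocol article*

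**What the plan says.** - **Main analysis.** Measurements and Analyses names the paired t test together with the "Wilcoxon test to compare the before and after means at a significance level of .05". Table 1 sets a null of equal means for time use and for coding quality. The time alternative is two-sided: "There is a significant time difference between using CAC and not using CAC for coding Swedish clinical notes".
- **Time endpoint.** It is defined only as "Time spent is the time it takes for a clinical coder to assign a code". Sample Size Calculation adds that "the same coders are measured twice on mean performance in time" and that "each sequence will consist of approximately 10 coding instances, giving extra power to the estimation of the sequence mean". No transformation is mentioned.
- **Size.** From a t-test power plot (Figure 2), "we aim to recruit up to 30 participants in total".
- **Who and what is timed.** Participants are those "who understand Swedish with any amount of coding experience". Short and long notes are both included. Of the long ones, Evaluation Outcomes says "Such cases take more resources than shorter and simpler texts" and expects the largest savings there.
- **Use of the result.** The Results overview bases the conclusion on two tests, one for time and one for quality. Principal Findings then reasons from whether each is significant.

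**The concern.** Two tests are fixed as the main analysis of one hypothesis, with no order between them. The document does not say when one replaces the other or what follows if only one is significant. The Results overview and Principal Findings assume a single answer per outcome, so in a discordant trial the plan gives no answer on time, and the more favourable result could be reported.

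The tests also have different targets. The t test concerns the mean difference. The signed-rank test concerns the pseudomedian of the differences, which equals the mean only under symmetry. Calling both a comparison of means is therefore wrong as written.

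The second part is conditional. Coders of any experience and notes of very different length make right-skewed times plausible. If an aid also saves a percentage of the time, differences in raw means are driven by slow coders and long notes, and a raw-scale test may miss a saving that a log-scale test would show.

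**Working it through.** **1. The plan's own figure.** The effect sizes and target power are only in Figure 2, which is not shown, so 30 can be neither confirmed nor refuted. A paired t test with n = 15 has 82.1% power at a standardised effect of 0.8. Doubling for two sequences gives 30, which fits the description of effects from upper medium to high. The sizing uses the t test alone.

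**2. Inputs.** From the protocol: 30 coders, about 10 notes per interface, two-sided .05, coder means as the unit. Assumed, because the protocol gives no SD or distribution: log-normal times, log-scale SD between coders 0.2–0.7 and per note 0.3–1.0, true time ratio r from 0.75 to 0.90 (1 under the null).

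**3. Model and tests.** For coder i, interface k (0 control, 1 tool) and note j, log T = b_i + k·log(r) + e_ijk. Let M_ik be the coder's mean time over 10 notes.
- Raw t: d_i = M_i1 − M_i0, t = mean(d)/(SD(d)/√30), 29 df.
- Wilcoxon: exact signed-rank on d_i. The rank total is 30·31/2 = 465; reject if W ≤ 137 or W ≥ 465 − 137 = 328.
- Log of mean: paired t on log(M_i1/M_i0).
- Mean of logs: paired t on the coder's difference in mean log time per note.

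**4. Results, uniform proportional saving (20,000 trials per row, %).**

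| SD coder/note | r | Raw t | Wilcoxon | Log of mean | Mean of logs | Raw tests disagree |
|---|---|---|---|---|---|---|
| 0.2/0.3 | 0.90 | 97.9 | 97.6 | 98.2 | 98.6 | 1.0 |
| 0.3/0.5 | 0.90 | 61.2 | 61.8 | 65.6 | 69.9 | 8.4 |
| 0.3/0.5 | 0.85 | 93.4 | 93.6 | 95.5 | 97.2 | 3.1 |
| 0.5/0.8 | 0.85 | 45.4 | 50.4 | 56.3 | 67.1 | 12.0 |
| 0.5/0.8 | 0.80 | 71.6 | 77.8 | 83.5 | 91.5 | 11.1 |
| 0.5/0.8 | 0.75 | 89.6 | 93.4 | 96.0 | 98.9 | 5.7 |
| 0.7/1.0 | 0.85 | 23.4 | 30.9 | 36.4 | 48.7 | 12.9 |
| 0.7/1.0 | 0.80 | 40.9 | 52.4 | 60.4 | 75.5 | 16.9 |
| 0.7/1.0 | 0.75 | 59.3 | 73.3 | 81.0 | 92.6 | 18.2 |

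The largest gap between raw t and mean of logs is 75.5 − 40.9 = 34.6 points. With SDs 0.3/0.5 it is at most 69.9 − 61.2 = 8.7. Log of mean recovers less: at most 81.0 − 59.3 = 21.7 points over raw t.

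**5. Type I error (r = 1).** Each raw test alone gives 4.3–5.2%, and log of mean 4.8–5.2%. Accepting either raw test gives 5.9, 6.2, 6.4 and 6.5% from least to most skew (5.8% with normal differences). Two independent tests would give 1 − 0.95² = 9.75%; these two are strongly correlated. They disagree in 2.1–3.6% of null trials.

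**6. Savings concentrated in long notes.** Further assumptions: note SD 0.3, five long notes per period taking twice as long, coder-by-interface SD 0.15, no saving on short notes and 25% on long ones. Power for raw t / Wilcoxon / mean of logs is 88/89/82% at coder/residual SDs 0.3/0.4, 75/79/76% at 0.4/0.5 and 48/54/54% at 0.5/0.7. If short notes are also 10% slower, it is 53/57/39% at 0.4/0.5. A separate simulation gave 78/80/73% and 58/60/39% for these two patterns of effect. In that simulation log of mean beat raw t in every setting with an effect, by about 0.5 to 14 points.

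**The case against.** **Power.** A reader might infer that the planned analysis loses substantial power. The documents do not support that without qualification. They give no SD, correlation or distribution, and the raw scale is itself inferred from the references to means. A transformation could sit in an analysis plan not shown. Log-normal times with the same percentage saving on every note favour the log scale by construction, and step 6 shows that mean log time per note can do worse than raw means under the protocol's own expectation about long notes. Averaging about 10 notes reduces skew, the Wilcoxon test recovers part of any loss, sessions are to be completed in one sitting, and an analysis by text length is planned. All of this stands, and it limits the power claim to a range under stated assumptions.

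**Two tests.** A reader might also infer serious inflation of the type I error. The cost is only about 1 to 1.5 points. It can be argued that the t test is implicitly primary, since the sizing rests on it, and that the Wilcoxon test is its usual companion. But the analysis section does not say so: it makes both the main analysis, at the same level. That is a stated rule fixed badly, not a detail left out.

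**Target.** A log-scale analysis answers a question about ratios rather than minutes. This is true, and is the price of the fix.

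**Conclusion.** The point holds in two parts of different strength.

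- **From the text alone:** each hypothesis has two unranked main tests, one of them wrongly described as comparing means, and the conclusion needs one verdict. Under the assumed log-normal times they conflict in about 3–15% of trials with a real effect. The figure reaches 18% in the most skewed setting and is close to nil where both tests have nearly full power.
- **Conditional:** if times are right-skewed and savings proportional, raw-scale tests lose about 0–10 points of power with mild skew and up to about 35 with strong skew, against the most favourable log-scale analysis. Which of these applies cannot be known from the protocol.

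This is worth correcting because the change is cheap, but it does not show that the trial is underpowered.

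**What to change.** Before the data are seen, name one primary test for time at two-sided .05. The preferred choice is a paired t test on the log of each coder's mean time per note under each interface, reported as a time ratio with 95% CI. Taking the log after averaging keeps the weight on long notes, where the protocol expects most of the saving; averaging log times note by note would not.

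Make the Wilcoxon test a sensitivity analysis, described as a test of location and not of means. Report mean minutes saved per note descriptively. State in one line which test is primary for coding quality as well.

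The cost is a change of analysis text, with no extra participants or data. The downside is that the headline result becomes a percentage change, with minutes as a supporting figure.
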